#### Primary outcome

The CPC (child version) is the primary outcome measure of the study [18]. This scale assesses post-traumatic stress symptoms in children aged 7 to 18 based on DSM-5 criteria [25]. It includes 21 items evaluating symptom frequency (e.g., intrusion, avoidance, hyperarousal) and 6 items assessing functional impairment. Responses are rated on a Likert scale from 0 (never) to 4 (daily), with higher scores indicating greater symptom severity. The scale has been validated in French with robust psychometric properties. Clinicians, blinded to group allocation, will administer the CPC to ensure consistency and reliability [26]. Time Frame: Baseline, immediately after completion of the program, and 3 months after completion of the program.

#### Secondary outcomes

– Evolution by the variation in the total symptom score on CPC of post-traumatic stress symptoms in children at baseline, immediately after completion of the program, and 3 months after completion of the program.– Evolution of post-traumatic stress symptoms in parents, at baseline, immediately after completion of the program, and 3 months after completion of the program using the Post-Traumatic Stress Disorder Checklist for DSM-5 (PCL-5). The PCL-5 is used to evaluate PTSD symptoms in parents [27]. It includes 20 items corresponding to DSM-5 diagnostic criteria, with scores ranging from 0 (no symptoms) to 80 (severe symptoms). Subscales assess intrusion, avoidance, cognitive and mood alterations, and hyperarousal. It has been validated in French with good psychometric properties. In the PCL-5, a score of 2 or more on any item (scale: 0 to 4) is considered clinically significant. The score can range from 0 (no symptoms) to 80 (maximum symptoms).– Correlation at baseline between CPC total score (child version) and variables from a socio-demographic and developmental questionnaire.– Correlation at baseline between CPC total score and presence of a pre-existing psychiatric or neurodevelopmental disorder prior to the TE assessed by the K-SADS.–Correlation at baseline between the CPC total score and trauma history (number of prior TEs) and parental trauma (LEC-5). The presence of one or multiple past traumatic exposures in one or both parents, will be assessed using the Life Event Checklist-5. The Life Event Checklist DSM-5 version [21] consists of a list of 16 potentially TEs based on Criterion A of PTSD in the DSM-5. For each event, the participant must indicate their level of exposure (experienced directly, witnessed, learned about, or work-related).– Correlation at baseline between CPC total score and parental PCL-5.– Correlation at baseline, immediately after completion of the program, and 3 months after completion of the program between CPC total score and CYRM-28 child version. Protective factors such as social and family support and the child’s skills are assessed using CYRM (one version for ages 7–10 and another for ages 11–17). The CYRM [22] is a globally used scale for measuring social and family support and the child’s skills. It was translated and validated in French by a Canadian team [23] and consists of 17 items assessing social and family support and the child/adolescent’s skills in daily life. The child version has two forms: one for ages 7–10 and another for ages 11–18. There is also a parent-report version that assesses their perception of the child’s social and family support and skills (one for ages 7–10 and another for ages 11–18).– Correlation between CPC total score and parental PTSD symptoms (PCL-5) at baseline, immediately after completion of the program, and 3 months after completion of the program.– Correlation between Child Posttraumatic Stress Checklist (CPC) total score and parental presence during the program period (weekly parental presence, 1 session per week, up to 8 weeks)]– Correlation between Child Posttraumatic Stress Checklist (CPC) total score and time elapsed before Child and Family Traumatic Stress Intervention (CFTSI) implementation. The delay before CFTSI implementation is the time, in days, between index trauma and the first CFTSI session.– Mean change in PTSD symptoms (PTSD-Rating Index) during the program period (weekly, up to 8 weeks). PTSD symptoms assessed using the PTSD-RI, clinician-rated, during each CFTSI session. Score ranges from 0 to 88: higher scores indicate more severe symptoms. This questionnaire, administered by clinicians, is integrated into CFTSI sessions and is used in each session as a tool to enhance symptom identification and communication.– Mean change during the program period (weekly up to 8 weeks) in MFQ score. MFQ score ranges from 0 to 66 (higher scores indicate more severe depressive symptoms). This questionnaire, administered by clinicians, is integrated into CFTSI sessions and is used in each session as a tool to enhance symptom identification and communication.– Concordance at baseline, immediately after completion of the program, and 3 months after completion of the program between child- and parent-reported post-traumatic symptoms via CPC child and parent version.– Concordance between child- and parent-reported child’s perception of social support and skills via CYRM child and parent version at baseline, immediately after completion of the program, and 3 months after completion of the program.

#### Other assessments

A detailed socio-demographic and early development questionnaire will be used to collect information about the child’s age, gender, family structure, socio-economic status, and developmental milestones. It will also include questions on prenatal, perinatal, and early childhood history, as well as previous medical or psychological interventions. The CPC will be used to evaluate the child’s history of exposure to TE, including physical and sexual abuse, natural disasters, accidents, and other adverse experiences. The questionnaire includes versions adapted for children and parents, ensuring comprehensive data collection. The K-SADS, a semi-structured diagnostic interview, will be used to assess pre-existing psychiatric or neurodevelopmental disorders in children. This tool is validated in French and will be administered at baseline to confirm eligibility and gather diagnostic data [20, 28]. The THQ [29], adapted by the founders of the CFTSI for adult use (assessing the parent’s own history of traumatic exposure) and for use by parents (assessing the child’s history of traumatic exposure as reported by the parent), is not the same version used for the secondary outcome measure. Instead, we used the clinically adapted version developed by the CFTSI founders, which we translated ourselves.

#### Intervention adherence and fidelity

Adherence will be monitored by tracking the number of sessions attended by participants in both the CFTSI and control groups. Completion of all five core sessions will be considered full adherence, while drop-outs will be documented for families attending fewer sessions. To monitor fidelity, all sessions will be recorded, and a sample of 20% of the recorded sessions will be reviewed and assessed by a supervisor trained in CFTSI, who will complete a structured observation form, developed for the CFTSI, to score which elements of the intervention have been carried out by the clinician and to what quality. Additionally, regular supervision and coaching sessions will take place with experienced and trained CFTSI supervisors of the Yale Child Study Center.

#### Family impact

Observations from joint sessions in the CFTSI group will provide qualitative data on parent-child interactions and the family’s ability to communicate about trauma-related symptoms. These interactions will be analyzed to evaluate changes in family dynamics over the course of the intervention.

#### Satisfaction questionnaire

At the end of the intervention (session 5 for the CFTSI group), parents and children will complete a satisfaction questionnaire to assess their perceptions of the intervention’s effectiveness and their overall experience.

### Randomization

At the inclusion visit, randomization will be conducted after verifying eligibility criteria and having obtained informed consent. The investigator will perform the randomization using the e-CRF system via Ennov Clinical^®^ software. Once the randomization is completed, the system will immediately generate the participant’s unique study identification number and assign them to either the control or experimental group. The site will then notify the investigator of the randomization result and group allocation.

### Sample size

According to Hahn’s (2019) [15] meta-analysis, the effect size (Hedge’s g) in favor of the CFTSI intervention ranged from 0.86 to 1.17 (*N* = 640 children). In a Cochrane 2016 meta-analysis, comparing all psychotherapies versus control (short-term standard care), on total PTSD symptoms, the effect size is −0.53 (CI95%: −0.94; −0.12) when looking at family therapies [30].

Taking this effect size of −0.53 with a power of 80% and a two-sided alpha risk of 5%, it is necessary to include 57 patients per group (NQuery software). Given an expected drop-out rate of around 20%, it is necessary to include 70 patients per group, i.e. 140 patients in total.

### Blinding

Although this is an open-label study, the investigators responsible for conducting assessments will remain independent of the intervention process and will not be involved in delivering the therapy. To minimize bias in outcome evaluation, parents and children will be reminded before each assessment not to disclose details regarding the type of intervention they received. Since this study evaluates non-pharmacological interventions, there is no procedure for unblinding a participant’s allocated intervention. Given the nature of the study, it was deemed unnecessary to establish specific unblinding circumstances or protocols.

### Data collection methods

All assessments will be collected for each participant in accordance with the e-CRF developed for the study. Data will be recorded by the investigator(s) or clinical study technician(s) involved in the trial, following the standardized procedures outlined in the protocol. Real-time quality control will be ensured through the use of the Ennov Clinical^®^ software platform, which complies with regulatory standards for clinical data management.

### Data management

The study data are entered into the e-CRF developed from the ENNOV CLINICAL software, which allows real-time quality control of the data. In order to meet regulatory requirements, this software complies with FDA recommendations concerning Computerised Clinical Trial Management Systems and electronic signatures, as well as standards (CDISC, ICH, GCP 2001/20/EC, etc.). Connection to the eCRF is via a password and a unique identifier for each user, which will only give access to patient data. An audit function is built into the software, enabling traceability of the data collected and any modifications made. The encrypted data will then be transmitted to the center responsible for data management via a secure internet connection. The e-CRF must contain all the information required by the protocol.

### Data processing

The individual data required to analyse the study must be:

– entered into the e-CRFs as they are obtained, whether they are clinical or para-clinical data.– anonymised by the investigator.– authenticated by an electronic signature from the investigator.– all data are entered, which means that missing data must be justified.

Initially, the data entered into the e-CRF is checked and validated by the Clinical Research Monitor on the basis of the source documents.

Secondly, the data manager performs additional computerised consistency tests based on the presence of non-standard, missing, aberrant or inconsistent data, which are performed regularly during patient recruitment and follow-up. All consistency tests are defined in advance in a set of specifications proposed by the data manager and validated by the investigator, the statistician, the CRA monitor and the study TEC. Each inconsistency identified in the e-CRF (‘Query’) is the subject of a request for correction or justification to the investigator (response to the ‘Queries’). The investigator undertakes to make himself available to the members of the research team and to provide them with any additional information required to resolve these errors. This information is recorded in the study database.

Once the study has been completed, i.e. the data required by the protocol and any additional data entered (self-questionnaires), and the data monitored and validated, the study database is frozen.

The Clinical Research and Epidemiology Unit (URCE) at Montpellier University Hospital is responsible for maintaining the database. The data is stored in ASCII format.

### Data coding

Data coding is integrated into the e-CRFs. Drugs are coded when they are entered using their international non-proprietary name (WHO ATC database). Recoding of certain data is carried out prior to analysis by the study biostatistician.

### Data storage

Computer files and monitoring of any changes are backed up and made available by the Montpellier University Hospital CER. Server location: The application and database are hosted on the following servers OVH (Datacenter certified ISO 27001).

### Access protection

Authentication/Identification for access to the application:

Profiles define the functions and types of information accessible to users;

Logical access control is by password: minimum 8 characters blocked after three unsuccessful attempts;

Parameters defined in the CSAdministrator module.

### Database freeze

The database is frozen in accordance with the URCE (Clinical Research and Epidemiology Unit) procedures. The freeze is documented by a database freeze certificate and occurs only after all data have been verified and all corrections requested from the investigators have been completed.

### Statistical methods

The statistical analyses will be detailed in a statistical analysis plan (SAP) finalized before the last patient in the study is included.

#### Descriptive analysis

A flow chart describing participant numbers during follow-up will be provided. It will describe the number of patients included, randomized in each arm, exited in each arm, and analyzable for the main analysis. Discontinuation causes will be reported for each arm.

Patient characteristics will be described overall and by group for the ITT population. Quantitative variables will be described using standard statistics: mean and standard deviation, median and interquartile range, minimum and maximum values. Qualitative variables will be described by the numbers of each modality and the corresponding percentages.

#### Analysis of primary endpoint

The analysis of the primary endpoint will be performed on an intention-to-treat basis. The primary endpoint (pre-post intervention variation in the child version of the CPC score) will be compared between the two groups using an analysis of covariance (ANCOVA) in order to adjust for the stratification criteria of the randomization. The effect size will be determined using Cohen’s d.

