**Methods:**

This study is a multicenter, evaluator-blinded RCT comparing CFTSI to supportive counseling. Eligible children (aged 7–17) must have experienced a TE within the past 45 days and exhibit at least one posttraumatic stress symptom. Exclusion criteria include severe cognitive impairment, ongoing abuse, or acute psychiatric emergencies.The CFTSI group will receive 5–8 structured, family-focused telehealth sessions targeting parent-child communication and coping. The control group will receive supportive counseling. The primary outcome is post-traumatic symptom reduction, assessed using the Child Posttraumatic Stress Checklist 3 months after completion of the program. Secondary outcomes include three-month symptom persistence, parental PTSD symptoms, and predictors of response. Analyses will use ANCOVA and regression models adjusted for baseline characteristics.

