#### Analysis of secondary endpoints

– Endpoints 1 (change in child CPC score between Baseline, immediately after completion of the program, and 3 months after completion of the program) and 2 (change in parent PCL-5 scores). The analysis will be carried out in the same way as for the primary endpoint.– Endpoints 3 (relationship between different participant characteristics and pre-intervention CPC score) and 4 (relationship between different participant characteristics and response to treatment).The factors associated with the CPC score will be analyzed using multiple linear regression. Determinants of response to treatment (change in CPC score) will also be analyzed using multiple regression.

– Endpoint 5 (concordance between child and parent CPC scores).The concordance between the CPC score obtained by the child and that obtained by the parents will be analyzed at each measurement time using the intraclass correlation coefficient (ICC) and its 95% confidence interval.

– Endpoint 6 (concordance between child and parent CYRM scores).The concordance between the CYRM score obtained by the child and that obtained by the parents will be analyzed at each measurement time using the intraclass correlation coefficient (ICC) and its 95% confidence interval.

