### Demographic and baseline characteristics

To ensure comparability, patient demographic and baseline characteristics will be summarized by group using descriptive statistics. For continuous variables, descriptive statistics (*n*, mean, standard deviation, standard error, median, minimum, and maximum) will be provided. For categorical variables, patient counts and percentages will be provided. Categories for missing data will be presented if necessary.

In the case of non-comparability for one or more parameters, an adjustment will be made on this/these parameter(s) for analysis of the judgment criteria. A multivariate linear regression model may be performed to account for potential confounders.

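### The primary ANCOVA of CPC change adjusts only for stratification factors that the article does not name, and does not pre-specify baseline CPC, which gives up precision

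*Protocol article*

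**What the plan says.** All references are to the protocol article.

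- **Analysis of primary endpoint.** The outcome is a change score: "The primary endpoint (pre-post intervention variation in the child version of the CPC score". The arms are compared "using an analysis of covariance (ANCOVA) in order to adjust for the stratification criteria of the randomization". No other covariate is given.
- **Randomization.** "The investigator will perform the randomization using the e-CRF system via Ennov Clinical^®^ software"; the system then issues a study number and will "assign them to either the control or experimental group". No stratification factor is named here or elsewhere in the article.
- **Analysis of secondary endpoints.** For change in child CPC and in parent PCL-5: "The analysis will be carried out in the same way as for the primary endpoint".
- **Abstract, Methods.** "Analyses will use ANCOVA and regression models adjusted for baseline characteristics". The characteristics are not listed.
- **Demographic and baseline characteristics.** "In the case of non-comparability for one or more parameters, an adjustment will be made on this/these parameter(s".
- **Statistical methods.** Detail is deferred to an SAP, which is not shown.

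Table 1 schedules both CPC and PCL-5 at baseline (T0).

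**The concern.** An ANCOVA of a pre-post change normally has the baseline value of the outcome as its main covariate. Here the stated purpose of the ANCOVA is to adjust for stratification criteria, and the article does not say what these are. A reader who runs the model as written cannot tell which covariates enter it and has no instruction to include baseline CPC.

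The article also points in three directions on adjustment: stratification criteria (primary endpoint section), unspecified baseline characteristics (abstract), and whatever turns out to be non-comparable between arms (baseline section). Under the third rule, whether baseline CPC enters the primary model would be settled only after the baseline table has been seen.

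Two things are at stake: precision on the primary endpoint and on the PCL-5 endpoint, and a primary model whose covariates are fixed in advance.

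**Working it through.** **Inputs.** Effect size 0.53 (absolute value), 80% power, two-sided 5%, 57 per group before drop-out, 20% drop-out, 70 per group (Sample size). The correlation r between baseline and follow-up CPC is not given, so I assume 0.3 to 0.7. The article does not say whether 0.53 is in SDs of the follow-up score or of the change, so I take both.

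**Step 1: the plan's own figure.** A two-sample t-test with d = 0.53, 80% power and two-sided 5% needs 56.86 per arm, i.e. 57, as stated. This calculation uses no baseline correlation. With 70 randomised per arm and 20% lost, 70 × 0.8 = 56 are analysed; t-test power at d = 0.53 is then 79.4%.

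**Step 2: variance.** With equal SDs (σ) at baseline and follow-up:

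- change score without baseline: 2σ²(1 − r)
- change (or follow-up) score with baseline as covariate: σ²(1 − r²)
- ratio: 2(1 − r)/(1 − r²) = 2/(1 + r)

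This gives 2/1.3 = 1.54, 2/1.5 = 1.33 and 2/1.7 = 1.18 at r = 0.3, 0.5 and 0.7.

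**Step 3: power if 0.53 is in follow-up-score SDs** (56 per arm, noncentral t). Effective d is 0.53/√(2(1 − r)) without baseline and 0.53/√(1 − r²) with it.

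| r | d without | power without | d with | power with |
|---|---|---|---|---|
| 0.3 | 0.448 | 65% | 0.556 | 83% |
| 0.5 | 0.530 | 79% | 0.612 | 89% |
| 0.7 | 0.684 | 95% | 0.742 | 97% |

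The 79% at r = 0.5 is the planned design at 56 instead of 57 per arm; it is not a loss against plan. By the normal approximation, 80% power needs 79, 56 and 34 per arm without baseline, against 51, 42 and 29 with it.

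**Step 4: power if 0.53 is in change-score SDs** (57 per arm, normal approximation). Without baseline, power is 80.8% at any r. With baseline, effective d is 0.53/√((1 + r)/2) and power is 93.9%, 90.4% and 86.6% at r = 0.3, 0.5 and 0.7.

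**Step 5: bias.** In 20,000 simulated trials per value of r (57 per arm, true effect −0.53), the change-score and baseline-adjusted estimates both average −0.53. They part only conditionally. In the 14% or so of trials where the intervention arm starts more than 0.2 SD higher (mean imbalance about 0.3 SD), the change-score estimate averages −0.74, −0.68 and −0.62 at r = 0.3, 0.5 and 0.7, while the adjusted one stays near −0.53. This matches the expected shift of (1 − r) × imbalance: 0.7 × 0.3 = 0.21 at r = 0.3.

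**The case against.** The strongest reply is that this is a condensed article. The Randomization section is silent on stratification; it does not say that there is none, and the primary endpoint section presupposes that there is some. The factors may stand in the full protocol. The SAP is still to come: "The statistical analyses will be detailed in a statistical analysis plan (SAP) finalized before the last patient in the study is included". The abstract's wording suggests that baseline adjustment is intended, and the non-comparability rule would bring in baseline CPC if the arms differed on it.

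Much of this stands, and it rules out several stronger readings:

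- **That the allocation is unstratified and the model collapses to a t-test on change.** That infers a fact from silence. The article supports only that the factors are not named.
- **That baseline CPC is excluded.** It is unnamed, not ruled out.
- **That the comparison suffers regression-to-the-mean bias.** Regression to the mean acts on both arms alike. Step 5 shows no bias over randomisations, only an error conditional on chance imbalance.
- **That this conditional error would go uncorrected.** Where baseline CPC clearly differed, the article's own rule would most naturally trigger adjustment, so error rates computed for such trials without adjustment do not describe the plan.
- **That the trial is underpowered.** A material shortfall below 80% needs both r below about 0.5 and 0.53 in follow-up-score SDs. The documents give neither.

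The reply does not remove the core. The primary endpoint section commits to an endpoint form and a reason for adjusting, and that reason refers to something undefined in the article. The non-comparability rule makes baseline adjustment depend on the observed data, and it recovers no precision in the majority of trials, where no imbalance is seen.

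**Conclusion.** The point holds as a matter of specification and precision. As written, the only stated adjustment in the primary model is for criteria that the article does not name. Baseline CPC is not pre-specified, and the article's three statements on adjustment do not agree. The same applies to PCL-5 through the secondary endpoint section.

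The cost is lost precision relative to an analysis that the trial can already do: a variance 18 to 54% larger for r between 0.7 and 0.3. In power, this is about 2 to 18 percentage points if 0.53 is in follow-up-score SDs, and about 6 to 13 points if it is in change-score SDs. These sizes rest on the assumed range of r, on equal SDs at the two times and on a linear relation between baseline and follow-up. The direction does not depend on where r falls in that range: leaving baseline out gains no precision at any r below 1. The validity of the comparison over randomisations is not in doubt.

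**What to change.** 1. In the primary endpoint section, pre-specify baseline CPC as a covariate in the ANCOVA, regardless of observed imbalance. With baseline in the model, the treatment estimate is the same whether the outcome is the change or the follow-up score.
2. In the secondary endpoint section, state baseline CPC for the child endpoint and baseline PCL-5 for the parent endpoint.
3. For these endpoints, replace the rule of adjusting for parameters found non-comparable with the fixed covariate list, and bring the abstract's description into line.
4. Name the stratification factors in the Randomization section and include them in the model; if there are none, delete the reference. The documents give no ground for adding a further factor, such as recruiting centre, unless it is a stratifier.

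The cost is a few sentences in the protocol and SAP. Both baseline scores are already collected at T0, no extra participants are needed, and the only statistical price is one degree of freedom per continuous covariate. The article puts the start of recruitment in December 2025, after its publication, and the SAP is to be finalised before the last inclusion, so the model can be fixed before any outcome comparison is seen.
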